## 5. Statistics

There will be three index tests used for clinical examination, 3D ultrasound imaging, and MRI of the ex vivo specimen. The reference standard will be the final histopathology result. Each case will undergo five margin measurements (anterior towards the apex of the tongue, posterior towards the base of the tongue, medial, lateral, and profound/deep margins) by three index tests and one standard reference. Tumor and specimen volume will be calculated for each case. The deep margin will be measured at equally distanced planes of imaging in every case, and the results will be correlated to the corresponding deep margin measurements from the reference standard.

The participants will be excluded from the final analysis in case of any technical issues such as non-feasibility to perform parallel slicing of the surgical specimen or patients with MRI contradictions (pacemaker, metal implants not compatible with MRI, etc.). The number of excluded participants will be reported as non-conclusive cases and will be excluded from the study.

Margin measurements (quantitative data in mm) and tumor and specimen volume measurements (quantitative data in ml) will be presented as an averaged value over two measurement repetitions, as described in Section 3.2. The measurement differences between the index tests and the reference standard will be compared by a paired *t*-test. The degree of correlation will be expressed using Pearson’s correlation coefficient, in which the index tests and the reference standard will be considered to be significantly correlated when *p* < 0.05. To evaluate the agreement between the index tests and the reference standard, we will also analyze the data using Bland–Altman plots, which show the mean difference between the two techniques with a 95% confidence interval. This allows for easy interpretation of whether the differences between the index tests and the reference standard are clinically relevant. Correlation between the plane-by-plane deep margin measurements obtained by the reference standard and the index tests will be evaluated by *t*-test, and the threshold for significance correlation will be *p* < 0.05. The correlation between the depth of invasion measurements (mm) from in vivo ultrasound and the ex vivo ultrasound will also be reported.

The intra- and interobserver variability will be quantified by calculating the intraclass correlation coefficient (ICC). The ICC measures the reliability of the measurements between the two observers and is the measure of the degree of agreement among the observers in their assessment of margin status.

We will also classify the data into three categories of positive (<1 mm), close (between 1–5 mm), and free (>5 mm) margins. For each included case, we will compare the accuracy of each index test by computing the proportion of correctly classified margins with respect to the reference standard class. We will use the McNemar test to determine if the proportions of categories in the index tests differ significantly from those of the reference standard (paired categorical data). The results will be considered statistically significant when *p* < 0.05, with a 95% confidence interval. 

The mean time spent on delineation by the operators will be recorded and reported in minutes. Data will be analyzed with commercially available software (RStudio Team-2023). RStudio: Integrated Development for R. RStudio, Inc., Boston, MA, USA.

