Following the surgery, two experienced head and neck surgeons will manually segment the tumor region on the 3D ultrasound images. This process will involve identifying and delineating the tumor boundaries based on the echogenicity differences between the tumor and the surrounding healthy tissue. Segmentation will be conducted using the ITK-SNAP segmentation software (www.itksnap.org (accessed 5 on July 2023)) [48], a widely used and validated tool for medical image segmentation. The surgeons will measure the smallest margin (anterior, posterior, lateral, medial, and deep margin). The segmentation process will be performed on approximately 10–15 equally distanced planes throughout the tumor volume. These planes will be selected to provide a comprehensive representation of the tumor and its spatial relationship with the surrounding tissue. The segmented regions from these planes will then be interpolated (using the interpolation tool in ITK-SNAP) to construct a 3D representation of the entire tumor structure. This approach allows for a detailed visualization and measurement of the tumor and its margins from multiple perspectives.

In addition to the overall tumor segmentation, the surgeons will measure the deep margin at every segmented plane. This step will provide a detailed plane-by-plane assessment of the deep margin, which is crucial for determining the adequacy of the resection. The measurements from the 3D ultrasound will then be correlated with the histopathology results to evaluate the accuracy of the ultrasound-based measurements.

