## 4. Clinical Outcome Definition

We will compare the surgical margin assessment in tongue cancer specimens by comparing three index tests (clinical examination, 3D ultrasound, and MRI) with the post-surgical histopathology assessments as the reference standard. 

The primary outcome will be reported as:The perioperative measurement of resection margins (mm) at five directions (Figure 1) with clinical exam and imaging compared to the post-surgical histopathology results (reference standard).The image-by-image comparison of the depth of invasion measurement (mm) from 3D ultrasound/MR imaging and histopathology slides.The depth of invasion (mm) comparison between in vivo and ex vivo ultrasound.The number of margins correctly classified as free (>5 mm), close (1–5 mm), or positive (<1 mm) margins by 3D ultrasound and MRI using histopathology findings as the reference.

The secondary outcome will be: The number of cases requiring adjuvant treatments (surgery or chemo/radiotherapy) due to T-site residuals.A change in tumor volume and resection margin measurements with 3D ultrasound imaging before and after formalin fixation.The time usage (minutes) and cost estimation for perioperative 3D ultrasound and MRI.

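### The plane-by-plane deep margins, about 10–15 per specimen, go into an ordinary t-test with no allowance for repeated measurement within a specimen; the five margins share the fault only if directions are pooled

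*Protocol article*

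**What the plan says.** **Planes.** Section 3.2.2: "The segmentation process will be performed on approximately 10–15 equally distanced planes throughout the tumor volume", and "the surgeons will measure the deep margin at every segmented plane". Section 5: "Correlation between the plane-by-plane deep margin measurements obtained by the reference standard and the index tests will be evaluated by" a t-test, with 0.05 as the threshold.

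**Images.** Section 4 lists an image-by-image comparison of depth of invasion with the histology slides among the primary outcomes. Section 5 names no separate method for it.

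**Margins.** Section 5: "Each case will undergo five margin measurements", by three index tests and the reference. For measurements in mm, a paired t-test sets each index test against histopathology. On association the plan says "The degree of correlation will be expressed using Pearson’s correlation coefficient", judged at p < 0.05; Bland–Altman plots carry a 95% interval. Margin categories are compared by McNemar's test. Section 4 counts margins ("The number of margins correctly classified as free", close or positive), whereas Section 5 takes the proportion correctly classified case by case.

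**What is averaged.** Values are averaged over two measurement repetitions, not over planes or directions. The only intraclass correlation in the plan is the one for observers.

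**The concern.** All the named tests, in their standard form, take each row of data as an independent observation. Planes through one specimen are not. They share one tumour, one set of image settings fixed at the specimen's centre before the sweep (Section 3.2.2), and one fixation process, whose effect on margins the plan itself treats as an outcome (Section 4). The Introduction also notes from earlier tracked-ultrasound work that tumour borders were harder to see in some specimens, which is error at specimen level.

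If specimens differ in their typical index-minus-reference difference, the planes of one specimen err together. The standard error computed from all planes is then too small, p-values are too small and intervals too short. What is at stake is the error rate and the coverage of the plane-level analysis, and of the depth-of-invasion outcome if it is handled in the same way.

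**Working it through.** **1. Number of independent units.** Section 6 gives 55% versus 16%, significance level 0.05 and 90% power. With unpooled variance and a two-sided test, n = (1.960 + 1.282)² × (0.55×0.45 + 0.16×0.84) / 0.39² = 26.4, so 27; and 27/0.90 = 30. The plan's figures reproduce (as a per-group size for independent proportions). They are numbers of cases; margins and planes do not enter.

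**2. Number of rows.** With 27 specimens: 27×10 = 270 to 27×15 = 405 planes, and 27×5 = 135 margins if directions are pooled.

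**3. Assumption.** The within-specimen intraclass correlation (ICC) of the index-minus-reference differences is not in the documents. I take 0.1 to 0.5.

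**4. Formulas.** Design effect DE = 1 + (m − 1)×ICC for m rows per specimen. A valid interval is √DE times as wide as the naive one. Effective rows = 27m/DE. True error of a nominal 5% test ≈ 2×[1 − Φ(1.96/√DE)]. A simulation of the naive t-test on pooled differences (27 specimens, 4000 runs per setting) checks the last formula.

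| m | ICC | DE | √DE | Effective rows | Error, formula | Error, simulated |
|---|---|---|---|---|---|---|
| 10 | 0.1 | 1.9 | 1.38 | 142 of 270 | 15.5% | 15% |
| 10 | 0.3 | 3.7 | 1.92 | 73 | 30.8% | 31% |
| 10 | 0.5 | 5.5 | 2.35 | 49 | 40.3% | 40% |
| 15 | 0.1 | 2.4 | 1.55 | 169 of 405 | 20.6% | 21% |
| 15 | 0.3 | 5.2 | 2.28 | 78 | 39.0% | 41% |
| 15 | 0.5 | 8.0 | 2.83 | 51 | 48.8% | 49% |
| 5 (pooled margins) | 0.1 | 1.4 | 1.18 | 96 of 135 | 9.8% | 9.5% |
| 5 | 0.3 | 2.2 | 1.48 | 61 | 18.6% | 18% |
| 5 | 0.5 | 3.0 | 1.73 | 45 | 25.8% | 26% |

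At ICC 0 the naive test is close to 5%. Analysing specimen means gives 4.5–5.8% throughout.

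**5. If the plane-level t-test is the test of a correlation coefficient.** Section 5 speaks of evaluating a correlation by a t-test, so this reading is open. With both measurements clustered at ICC 0.1/0.3/0.5, the simulated error is 6/15/27% for 10 planes and 7/20/35% for 15.

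**6. Other tests on pooled margins (m = 5).** Pearson: 5.7/9/16%, about 5–17% allowing for simulation noise. McNemar, assuming 40% discordant pairs: 8/17/21%.

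**7. What can offset this for pooled margins.** When fixed biases between directions have an SD equal to the within-direction SD, the pooled t-test's simulated error falls to 2.5% at ICC 0.1 and 8% at ICC 0.3.

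**8. If each direction is tested alone.** There is one value per specimen and no clustering, but there are five tests: 1 − 0.95⁵ = 23% chance of at least one false positive if the tests are independent.

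**The case against.** **Pooling of the five directions is not stated.** A reader might infer from the margin count in Section 4 that 135–150 margins enter one test, and hence that the intervals of all the primary outcomes are too narrow. The documents do not support that as fact. Section 4 speaks of measurement in five directions, Section 5 of a proportion for each case, and Section 6 sizes the study in cases. Tested one direction at a time, or summarised per case, the margins have no clustering problem. This objection stands, and limits the margin part to a conditional one.

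**The sign of the correlation is not given.** Opposite margins may err in opposite directions: a shift in the outlined tumour lengthens one and shortens the other. Fixed direction biases also work against inflation (step 7). This stands for pooled margins. It has much less force for deep margins on successive planes of one specimen.

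**Shared readers are a weak cause.** Imaging and histology are each read by two observers. If the same pair reads every specimen, their average bias is common to all patients and creates no within-specimen correlation. This stands, and I do not rely on it.

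**Matched planes may be fewer.** The 10–15 planes are ultrasound planes. Histology is sliced at about 2 mm (Section 3.2.4), so 10–15 matched pairs need roughly 20–30 mm of tumour along the slicing axis. Small tumours give fewer pairs and less inflation.

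**The plane-level deep margin is not a listed primary outcome.** True; the image-by-image item in Section 4 is depth of invasion.

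**It could be left to an analysis plan.** Not for the planes: the article itself names the test and the threshold.

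**Conclusion.** The point holds for the plane-level deep margins. As written, repeated planes per specimen enter an ordinary t-test at p < 0.05 without a specimen-level method. With 27 specimens and an assumed positive ICC of 0.1–0.5, a t-test on pooled differences has a true error of about 15–40% with 10 planes and 21–49% with 15, and naive intervals are too short by a factor of about 1.4–2.8. The correlation reading of the test gives smaller but still inflated errors. The image-by-image depth-of-invasion outcome is affected in the same way if images are analysed as separate rows with these tests.

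For the five margins the conclusion is conditional. If directions are pooled, the paired t-test error would be about 10–26% and Pearson's about 5–17% over the same ICC range, and less where direction biases or opposite-signed errors offset it. If each direction is tested alone, the issue is five tests rather than clustering. The defect that can be stated firmly here is that the unit of analysis is not fixed.

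The sizes rest on the assumed ICC. Mean differences and proportions correct are largely unaffected; what fails is their stated precision and the p-values.

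**What to change.** **Planes and images.** Make the specimen the cluster: a linear mixed model of the index-minus-reference difference with a specimen random effect; Bland–Altman limits in the repeated-measures form, with between- and within-specimen variance components; and a within-specimen correlation if a correlation is kept. State how many planes are matched to histology per specimen.

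**Five margins, mm.** Choose one and say so: analyse each direction separately with one value per specimen, acknowledging the five tests; or pool, with direction as a fixed effect and specimen as a random effect.

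**Classification.** Analyse the per-case proportion correct, or use a clustered McNemar test, GEE with the specimen as cluster, or a bootstrap that resamples specimens.

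**Cost.** Analysis wording only, with no new patients or measurements. Intervals will be wider, but valid.

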### 3.2. Perioperative Assessment of Margins 

#### 3.2.1. Surgical Specimen Examination by the Surgeon

A standard examination of the surgical specimen will be performed in the operation theater by the surgeon in order to assess the margins after resection. This usually includes inspection and palpation of the surgical specimen to assess if there are close/positive margins. Additionally, the surgeon will evaluate the margins at five specific areas (anterior, posterior, medial, lateral, and profound) and estimate the closest distance in mm from the tumor to the resection (free margin) for each area. See Figure 1 for the schematic of the definition of the margin measurement directions.

Then, the surgeon will attach the resected specimen to a piece of cork using pins and will mark the directions.

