#### 3.2.3. MRI Scan of the Surgical Specimen in the Radiology Department

Immediately after the tumor resection, clinical examination by the surgeon, and the 3D ultrasound scan at the operation theater, the ex vivo surgical specimen will be transferred to the radiology department to allow for the acquisition of an MRI scan. The specimen will be oriented to maintain the same orientation as the 3D ultrasound scan. The surgical specimen pinned to the cork will be enclosed in a plastic box to ensure a stable positioning of the specimen and to minimize the possible pollution at the MRI setup.

A 1.5T MRI scan (Artist, GE Healthcare) will be performed using a wrist radiofrequency (RF) coil and a scan protocol with T2-weighted 2D MRI (1.0 mm slice thickness). The total examination time will be approximately 15 min. Two radiologists consultants will assess the surgical margins and the tumor region on the MRI scans over two rounds, similar to the procedure explained at Section 3.2.2.

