#### 3.2.4. Tissue Preparation and Histopathology

After conducting the MRI scan in the radiology department, the surgical specimen will be returned to the pathology department for formalin fixation. 

In the pathology department, the samples will be treated using standard procedures to create formalin-fixed, paraffin-embedded (FFPE) blocks of tissue. The samples are first formalin-fixed with 10% formaldehyde for 24 h. Before starting the slicing procedure of the specimen by the pathologist, the formalin-fixated specimen will again undergo 3D ultrasound. Then a pathologist will perform parallel slicing, with almost equal intervals (~2 mm). The slices are then transferred to cassettes for further processing and embedded in paraffin to form FFPE blocks, which are cut at 4 μm and mounted on glass slides. Afterwards, the slides will be stained with hematoxylin and eosin (H&E) to visualize the tissue under the microscope. Two pathologists will assess the surgical margin status and will delineate the tumor on the slides. The tumor volume in milliliters (mL) will be estimated by the multiplication of the tumor area per slice and the cutting intervals. The pathologist will also measure the smallest margin at the posterior, anterior, lateral, medial, and profound directions (as described in Figure 1). The average measurement obtained by the two pathologists will be considered as the gold standard.

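### Margins are analysed as two-read means, but only imaging has a second read described, so imaging and the surgeon are compared descriptively on unequal numbers of reads

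*Protocol article*

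**What the plan says.** Section 5 (Statistics) fixes one rule for margins and volumes: they "will be presented as an averaged value over two measurement repetitions, as described in Section 3.2". It exempts no index test. The paired t-test, Pearson correlation and Bland–Altman analysis follow in the same paragraph, and the three-class analysis follows shortly after by "computing the proportion of correctly classified margins with respect to the reference standard class". Apart from the ICC, no analysis of unaveraged margins is named.

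Section 3.2, to which the rule points, describes the reads as follows:

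- Clinical examination (3.2.1): "the surgeon will evaluate the margins at five specific areas", with one estimate in mm per direction. No second examiner or repeat is described.
- 3D ultrasound (3.2.2): "two experienced head and neck surgeons will manually segment the tumor region on the 3D ultrasound images". No rounds are described.
- MRI (3.2.3): "Two radiologists consultants will assess the surgical margins and the tumor region on the MRI scans over two rounds", said to resemble the ultrasound procedure.
- Histopathology (3.2.4): "The average measurement obtained by the two pathologists will be considered as the gold standard".

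**The concern.** The research question in Section 2 sets 3D ultrasound against clinical examination and MRI, and the Discussion asks whether ultrasound does better than both. Averaging two reads removes part of the random reader error. If imaging is averaged and the surgeon is not, part of any advantage in limits of agreement, correlation or class accuracy comes from the number of reads and not from the modality.

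There is a second consequence. The technique is proposed for use during surgery. If one operator takes one reading there, a two-read mean describes a more precise procedure than the one in use.

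The rule is also not fully determined. MRI has two readers and two rounds, while ultrasound has two readers and no stated rounds. The two repetitions could therefore be two readers or two rounds, and for the clinical examination there is no described second read to average.

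**Working it through.** **Inputs from the protocol.** The averaging rule is in Section 5 and the reads per test are in Sections 3.2.1–3.2.4. The case mix in the Introduction is 10% positive and 74% close, leaving 100 − 10 − 74 = 16% free. The cut-points are 1 mm and 5 mm. The protocol gives no reader SD, no ICC and no share of error common to both reads. Those are assumptions below. It also gives no figure of its own on this point to reproduce, and the sample size of 27 (30 with drop-out) does not depend on the number of reads.

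**1. Limits of agreement.** Let a share s of the error variance be common to both reads. The SD of a two-read mean relative to one read is √(s + (1 − s)/2).

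- s = 0: 0.71, so limits narrow by 29%
- s = 0.25: 0.79, or 21%
- s = 0.50: 0.87, or 13%
- s = 0.75: 0.94, or 6%

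The 29% is a ceiling. It needs independent read errors and a reference without error.

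**2. Correlation.** Averaging two reads multiplies r by √(2/(1 + ICC)): about 1.15 at ICC 0.5, 1.08 at 0.7 and 1.03 at 0.9. As an illustration, take true margins with mean 4 mm and SD 2.5 mm floored at zero, a pathologist reader SD of 0.5 mm and ICC 0.7. A single read gives a Bland–Altman half-width of 3.1 mm and r = 0.83. The two-read mean gives 2.3 mm and r = 0.90.

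**3. Three-class accuracy, case mix.** A gamma distribution with shape 2.46 and scale 1.28 reproduces 10/74/16%. Single-read error SD is 1.5 mm with no systematic error. One read classifies 71% correctly. The mean of two gives 78.7% (s = 0), 76.0% (s = 0.3) or 74.5% (s = 0.5). The gain is about 3–8 points, and about 2 points at s = 0.75.

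**4. Three-class accuracy, per margin.** The 10/74/16% mix is per case, whereas Section 5 classifies five margins per case. If case status is the smallest of five independent margins (an assumption), the share of single margins above 1 mm is 0.90^(1/5) = 0.979 and above 5 mm is 0.16^(1/5) = 0.693. That is about 2% positive, 29% close and 69% free. A gamma fitted to this mix, with the same 1.5 mm SD, gives 86.1% for one read. The mean of two gives 90.1% (s = 0), 88.7% (s = 0.3) or 87.8% (s = 0.5). The gain is about 2–4 points.

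**5. Systematic offset.** Averaging leaves it untouched. With the margin distribution of step 2, reader SD 1.5 mm and an error-free reference, accuracy for one read against two is:

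- 0 mm offset: 73.6% against 80.8%
- 1 mm: 70.0% against 74.0%
- 2 mm: 59.9% against 59.7%
- 3 mm: 49.2% against 46.9%

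On the per-margin mix of step 4, the gain is under 0.5 points when imaging reads 2 mm too wide.

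**6. Mean difference.** The expected difference is the same for one read and for the mean of two. Only its standard error shrinks, so a true imaging bias becomes easier to detect.

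**The case against.** The strongest reply is that the asymmetry is inferred. Section 5 exempts no test, Section 3.2.1 does not rule out a second clinical estimate, and a condensed article may leave the number of reads to a fuller document. This stands as a limit on certainty. It does not remove the point, because Section 5 refers to Section 3.2 for the repetitions and Section 3.2 describes none for the surgeon.

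It can also be said that a two-reader mean is a legitimate quantity if labelled, and that the planned intra- and interobserver ICC will show how far single reads differ. Both are fair. But the ICC does not give a reader the single-read limits or class accuracy to put beside the surgeon's.

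A reader might infer that the formal comparison with the surgeon is biased toward imaging. The documents do not support that. Section 5 states: "The measurement differences between the index tests and the reference standard will be compared by a paired" t-test. The McNemar test likewise sets each index test against histopathology, and no test of imaging against the surgeon is planned. The classification item among the primary outcomes covers only "margins by 3D ultrasound and MRI using histopathology findings as the reference". Ultrasound against MRI is even-handed if both use two-read means.

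A reader might also pool both MRI readers and both rounds into four reads and expect limits 50% narrower. Section 5 says two repetitions, and no rounds are described for ultrasound, so that figure has no footing in the text.

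Finally, imaging before fixation is compared with histopathology after fixation, and the protocol itself measures how fixation changes margins. A systematic offset is therefore plausible, and it would reduce or remove the gain in class accuracy.

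**Conclusion.** The concern holds in a limited form. As described, imaging is analysed on two-read means and the clinical examination on one read, so the descriptive comparison of limits of agreement and correlation rests on unequal numbers of reads. The same is true of class accuracy, where the gain arises only when systematic error is small. The imaging figures would look better than one reader's performance. The mean difference is not improved, and the tests against histopathology are not biased toward imaging. Averaging the two pathologists is no part of the problem, since that reference is common to all three tests.

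The size cannot be derived from the protocol. At an assumed single-read SD of 1.5 mm, with up to half of the error variance shared between reads and no offset, class accuracy rises by roughly 2–8 points, or 2–4 if the case mix is converted to single margins assuming independence. Limits due to random error narrow by at most 29%. With an offset of about 2 mm there is little or no gain in class accuracy.

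**What to change.** In Section 5, make the accuracy, agreement and classification results used to compare ultrasound, MRI and the surgeon single-read. Use each reader's first-round value, reported per reader or in a mixed model with a reader effect. Label the averaged read as a secondary analysis, and state whether the average is over readers or over rounds. Keep the two-pathologist mean for the reference standard.

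The cost is a change of wording and a little more analysis. The single reads are already needed for the ICC, so data collection and sample size do not change. Reported imaging accuracy may look slightly less favourable.

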## 2. Research Question

In patients surgically treated for oral tongue squamous cell carcinoma, what is the accuracy of 3D ultrasound compared to clinical examinations and MRI in the assessment of tumor resection margins?

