## 8. Discussion

Earlier studies have demonstrated the advantages of 2D ultrasound-guided tongue SCC resections [7,18,51]. This trial aims to explore whether a novel 3D ultrasound imaging technique of the tongue tumor offers a diagnostic rate higher than that obtained using MRI and clinical examination by the surgeon. If so, implementation of surgical margin assessment using 3D ultrasound may increase the free margin rate in tongue cancer surgery. This will improve the treatment of tongue tumor patients and will reduce healthcare costs. 

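### The research question compares 3D ultrasound with MRI and clinical examination, but every significance test fixed for the margins compares one index test with histology

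*Protocol article*

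**What the plan says.** Section 2 (Research Question) of the protocol article asks "what is the accuracy of 3D ultrasound compared to clinical examinations and MRI in the assessment of tumor resection margins". Section 8 (Discussion) gives the direction: the trial explores whether the new technique "offers a diagnostic rate higher than that obtained using MRI and clinical examination by the surgeon". Both statements are about one index test against another.

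Section 4 lists the mm margins in five directions as the first primary outcome, "with clinical exam and imaging compared to the post-surgical histopathology results (reference standard").

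Section 5 then fixes these analyses of mm data:
- "The measurement differences between the index tests and the reference standard will be compared by a paired" t-test.
- Pearson's coefficient, where "the index tests and the reference standard will be considered to be significantly correlated when" p < 0.05.
- Bland–Altman plots: "To evaluate the agreement between the index tests and the reference standard".
- For the deep margin by plane: "Correlation between the plane-by-plane deep margin measurements obtained by the reference standard and the index tests will be evaluated by" a t-test, again at 0.05.
- "The correlation between the depth of invasion measurements (mm) from in vivo ultrasound and the ex vivo ultrasound will also be reported".

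For margin categories, Section 5 reports the proportion correctly classified by each index test and uses McNemar's test of each index test's categories against those of the reference standard.

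**The concern.** A claim that ultrasound is more accurate than MRI or the surgeon's examination needs an estimate of the difference in accuracy between two index tests, with its uncertainty. The null hypothesis of each planned paired t-test is that one index test has zero mean error against histology. No planned test has the null hypothesis that two index tests have equal error. The between-test answer would have to be pieced together from three separate comparisons with histology, and one significant and one non-significant result do not amount to a test of the difference.

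The paired t-test is also a poor stand-in for accuracy. It responds to mean bias relative to scatter, so for a given bias a more precise test is more likely to be flagged. A shared bias is plausible here: all three perioperative assessments are made on the fresh specimen, histology is read after 24 hours in formalin, and the protocol lists change in margin measurements with fixation as a secondary outcome.

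At stake is the trial's headline conclusion, which has no planned test or interval behind it. The measurements themselves are unaffected.

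**Working it through.** **Step 1. Line up question and analyses (all from the protocol article).**

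| Analysis in Section 5 | What is compared | Tests ultrasound against MRI or surgeon? |
|---|---|---|
| Paired t-test, margins in mm | index test v histology | no |
| Pearson correlation, p < 0.05 | index test v histology | no |
| Bland–Altman plots | index test v histology | no; descriptive |
| Plane-by-plane t-test, deep margin | index test v histology | no |
| Depth-of-invasion correlation | in vivo v ex vivo ultrasound | no; ultrasound against itself, and not a margin |
| Proportion correctly classified | each index test v histology class | side by side, no test or interval |
| McNemar | index test v histology | no |

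The mismatch is complete for the margin outcomes and needs no simulation.

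**Step 2. Does the sample size fill the gap?** Section 6 uses free-margin rates of 55% and 16%, alpha 0.05 and 90% power. With the unpooled formula, two-sided:

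n = (1.960 + 1.282)² × (0.55×0.45 + 0.16×0.84) / 0.39² = 26.4, so 27; and 27/0.9 = 30.

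The stated figures reproduce. But the calculation concerns how often margins are free with and without ultrasound. That is neither error in mm nor classification accuracy, and Section 5 has no matching test.

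**Step 3. What would the separate t-tests show?** The article gives no bias or SD for any method, so the values below are assumptions. Set-up: n = 27, one margin per specimen, normal errors against histology, correlation 0.3 between the two tests' errors, 20,000 simulated trials. The planned approach is a t-test of each test's error against zero. The direct approach is a paired t-test on the within-specimen difference in absolute error.

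Analytic check: power to flag a bias b with error SD s comes from the noncentral t with 26 df and noncentrality (b/s)√27. For b = 0.5 and s = 1 this is 2.60, giving 71%. For b = 0.5 and s = 2 it is 1.30, giving 24%. The same bias is flagged three times as often in the more precise test.

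| Ultrasound bias, SD (mm) | Comparator bias, SD (mm) | Only ultrasound flagged | Only comparator flagged | Direct test favours ultrasound |
|---|---|---|---|---|
| 0, 1 | 0, 2 | 5% | 4% | 90% |
| 0.5, 1 | 0.5, 2 | 51% | 4% | 82% |
| 0.5, 0.8 | 0.5, 2.5 | 72% | 1% | over 99% |
| 0, 1 | 1, 1 | 0% | 95% | 47% |
| 0.2, 1 | 1.5, 1.5 | 0% | 83% | 97% |
| 0, 1 | 1.5, 2 | 0% | 92% | 99% |

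Ultrasound has the smaller mean absolute error in every row. In the first it is half the comparator's: 0.80 against 1.60 mm. For two identical tests (bias 0.5, SD 1), exactly one is flagged in about 35% of trials, whereas the direct test rejects in 5%. For error correlations from 0 to 0.5, the second row's 51% runs from 49% to 54%.

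**Step 4. Can the existing sample support a direct contrast?** With 90% power and two-sided 0.05, the detectable standardised within-specimen difference is (1.960 + 1.282)/√27 = 0.62, or 0.59 at n = 30 (normal approximation).

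**The case against.** The strongest reply has four parts.

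1. The article never says that the three t-test verdicts will be set against each other, or that a non-significant result means a more accurate test. This stands. A reader might infer that the plan will rank the tests backwards by p-value. The document contains no such rule, so the figures in Step 3 show only what would follow if the results were read that way.

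2. Bland–Altman plots are planned, and they display the spread of errors. This stands too. In the first three rows of Step 3, comparing the SDs of the differences puts ultrasound first in essentially every simulated trial. A reader who looks at the plots would see which test is tighter. The plots still give no interval or test for the difference between index tests.

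3. The misleading pattern depends on the assumed biases. This stands. A reader might infer that the separate tests have almost no chance of favouring a better ultrasound. The last three rows refute that as a general statement: when the comparator is more biased, the pattern is correct in 83–95% of trials, and in one of those rows it points the right way more often than the direct test does (95% against 47%).

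4. The outcome is defined against histology, accuracy is to be compared through proportions correctly classified, and a condensed article may leave contrasts to a fuller plan. This stands only in part. A between-test comparison is indeed foreseen on the classification scale, but only as proportions side by side. Further contrasts may exist elsewhere. Yet the article names its tests, their pairings and their threshold, and those do not match the question it poses.

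**Conclusion.** The point holds in this form: the research question and aim compare index tests with each other, while every significance test fixed for the margins, in mm and in categories, compares one index test with histology. The descriptive analyses permit an informal comparison without a test or confidence interval for the difference. This conclusion rests on the text alone.

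The risk of a misleading reading is conditional. Under a shared 0.5 mm bias and SDs of 1 and 2 mm, only the more precise test is flagged in about 50% of trials; with a more biased comparator, the separate tests give the correct pattern in 83–95%. These figures assume normal errors, one margin per specimen and n = 27, and the document supplies no error sizes with which to choose between them. The change should be made before analysis, because without it a statement that ultrasound is more accurate would rest on no planned inference.

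**What to change.** Add to Section 5, as the analysis that answers the research question:

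- For each specimen and index test, compute the absolute error against histology in each of the five directions.
- Estimate two within-specimen differences in mean absolute error, ultrasound minus MRI and ultrasound minus clinical examination, each with a 95% confidence interval and a paired test. Either average the five directions per specimen first, or use a mixed model with a patient effect.
- Base any conclusion that one test is more accurate than another on these two contrasts.
- State that the t-tests against histology describe the bias of each index test only and are not used to compare index tests.

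The cost is a few sentences and a short extra analysis. Every specimen is already to be measured by all three index tests and by histology, so no patients, readings or procedures are added.
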